## 2.3 Potential Risks and Benefits

### 2.3.1 Potential Risk

- **Risk to the participant**

Untreated sleep-related breathing disorders as an aggravating factor for neuropathic pain, cardiovascular dysfunction and spasticity following spinal cord injury

- a) There may be some minor discomfort from wearing the ApneaLink Sleep Breathing Monitor.
- b) There may be some minor disturbance of participant's usual sleep on the night that she/he is wearing the ApneaLink device.
- c) Participants may learn something about their sleep that they were unaware of, such as their probability of having a sleep disorder, which could cause some anxiety or discomfort. Those participants who are diagnosed with moderate-to-severe SRBD are expected to try on and adhere to CPAP therapy. If the participant refuse to be adherent to CPAP therapy, the healthcare professional caring for them is required by law to report the diagnosis to the Ministry of Transportation of Ontario that likely will suspend the participant's driving privileges.
- e) Blood collections can sometimes cause bruising, pain, or very rarely, loss of consciousness.
- f) Participants may learn something about their health related to abnormal blood test that they were unaware of, which may require further investigations and treatment by the participants' family physician; this could cause some anxiety or discomfort.

- **Risks to the community/public**

To the best of our knowledge: none.

- **Risks to the institution**

To the best of our knowledge: none.

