### **3.3 Study Hypothesis**

- (a) Individuals with SCI and untreated SRBDs more frequently develop more severe neuropathic pain;
- (b) Individuals with SCI and untreated SRBDs develop more significant cardiovascular dysfunction (i.e., reduced heart rate variation, more frequent episodes of autonomic dysreflexia during sleep);
- (c) Individuals with SCI and untreated SRBDs more frequently develop more severe spasticity.

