#### **4.1.1 Primary Outcome measures:**

- a) The presence and intensity of neuropathic pain as assessed using the Visual Analog Scale (VAS; range: 0 to 100) and daily amount of analgesics (pregabalin, neurontin, opioids, etc.);

Untreated sleep-related breathing disorders as an aggravating factor for neuropathic pain, cardiovascular dysfunction and spasticity following spinal cord injury

- b) The cardiovascular activity during sleep based on the peripheral arterial tone and overall heart rate variability as recorded using the Bittium Faros™ 180 device and Caretaker™ Medical cNIBP monitor device;
- c) The number of episodes of autonomic dysreflexia during sleep and their association with apneas and hypopneas by combining the recorded data from the ApneaLink™, Bittium Faros™ 180 device and Caretaker™ Medical cNIBP monitor devices;
- d) The degree of spasticity in the upper and lower limbs as assessed using the Modified Ashworth Scale;
- e) Serum CRP level.

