#### **4.2 Description of the type/design of the study**

This is 3-year cross-sectional, prospective study.

- (1) Individuals with SCI frequently decline to stay overnight to complete formal polysomnography due to their concerns about availability of proper support, funding for attendants and the accessibility of the sleep disorder clinics. Given this, we decided to use a home-based or hospital-unattended sleep test (ResMed ApneaLink Air™) that is a practical, less costly, validated and reliable surrogate for diagnosis of the SRBDs. A trained research assistant from Sunnybrook Health Science Centre with expertise on the setting up and use of ResMed ApneaLink™, Bittium Faros™ 180 and Caretaker™ Medical cNIBP monitor devices will be available to assist the participants who have questions or problems with setting up the sleep apnea testing. The process for the technical support for the home based-sleep study will include the following steps:
  - (a) The research assistant from Sunnybrook Health Science Centre will receive a notification by phone from the research coordinator from Lyndhurst stating that a new participant will undergo home-based sleep studies. The study participant identifying number (i.e. “study participant ID #...”) along with their address and minimal clinical information (only level and severity of spinal cord injury) will be provided.
  - (b) The study participant will receive the name and phone number of the research assistant from Sunnybrook Health Science Centre and will be instructed to call them if there are any questions or concerns only during home-based sleep study (12 hours overnight support).
  - (c) If the study participant is unable to set up the home-based sleep study devices, they will be offered to receive a visit from the research assistant at their residence. If the study participant agrees, the research assistant will provide technical support at their residence.

Untreated sleep-related breathing disorders as an aggravating factor for neuropathic pain, cardiovascular dysfunction and spasticity following spinal cord injury

If the study participant disagrees and the setting up is not possible, the study participant will be withdrawn from the study.

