## **5.2 Exclusion criteria:**

- Patients with a non-traumatic spinal cord disease at risk for disease recurrence during the study (*e.g.*, demyelinating spine diseases such as neuromyelitis optica and multiple sclerosis, spinal cord malignancy); of note, patients with other causes of non-traumatic spinal cord disease are eligible for this study.
- Concomitant significant diseases of the central nervous system causing neurological deficits (*e.g.*, concomitant traumatic brain injury, stroke, dementia, Parkinsonism, multiple sclerosis)
- Preinjury chronic pain (*e.g.*, fibromyalgia)
- Psychiatric disorders that could affect the home-based sleep study using the ApneaLink™ and cardiovascular evaluations.
- Neuromuscular diseases (*e.g.*, myasthenia gravis)
- Current substance misuse
- History of primary hypersomnia (*e.g.*, narcolepsy, idiopathic hypersomnia). Of note, hypersomnia is defined as prolonged sleep periods (*i.e.*, more than 10 hours per night).

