## **7. Statistics**

The baseline characteristics and outcomes measures among the four study groups will be analyzed using the Kruskal-Wallis test (non-parametric data) or ANOVA (parametric data). Study groups will also be compared using Fisher exact test regarding categorical variables. The costs of the home-based sleep study will be compared to the costs of the polysomnography using Mann-Whitney U test. Sample size and feasibility: Using pain (VAS) as the primary outcome measure, an estimated sample size of 10 subjects per group is required to detect a "minimal clinically important difference" of at least 25 mm in the VAS with a minimum power of 90% and a significance of 5% for 2-sided comparison tests.

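### Primary outcome 4.1.1(c) counts dysreflexia episodes with no time denominator, so recording hours that differ by SRBD group can create or hide a group difference

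*Protocol*

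**What the plan says.** Under "Primary Outcome measures", item (c) of Protocol Section 4.1.1 begins "The number of episodes of autonomic dysreflexia during sleep". It adds the association of these episodes with apneas and hypopneas, to be obtained "by combining the recorded data from the ApneaLink™, Bittium Faros™ 180 device and Caretaker™ Medical cNIBP monitor devices". No unit of time is attached.

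Section 7 states: "The baseline characteristics and outcomes measures among the four study groups will be analyzed using the Kruskal-Wallis test", with ANOVA as the parametric alternative. Section 11 points to Section 7 for the analysis methods.

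The hypothesis served is 3.3(b), which expects "more frequent episodes of autonomic dysreflexia during sleep" in people with untreated SRBDs.

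On observation time, the protocol says little:
- Section 2.3.1 speaks of possible disturbance "on the night that she/he is wearing the ApneaLink device", which implies a single night.
- Section 4.2 mentions "12 hours overnight support", but this is telephone help and not recording length.
- Section 5.2 mentions "more than 10 hours per night", but only to define the hypersomnia that excludes a person.
- No minimum usable time is set. Section 11 asks only that missing data be explained.

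**The concern.** A number of episodes measures frequency only if people are observed for comparable times. Here the test is unattended, at home or in hospital, and the count needs data from three devices together, so losing any one signal shortens the usable period. Observed hours will therefore vary between people.

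The important question is whether they also vary between SRBD groups. They might, through fragmented sleep, lost sensors or a different mix of home and hospital testing. Section 2.1 reports SRBDs more often in tetraplegia (48-91%) than in paraplegia (13-63%), so the groups may also differ in injury level. The documents do not say whether any of this affects usable hours, and they contain nothing that would prevent or reveal such an imbalance.

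If the severe group yielded fewer hours, a truly higher episode rate could be cancelled in the counts. Equal true rates could also appear as a difference. Either would distort the between-group result for a primary outcome.

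**Working it through.** **No figure of the plan to reproduce.** The only sample-size statement (Section 7) concerns VAS pain and gives 10 per group. There is none for dysreflexia.

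**Inputs from the protocol.** Four groups, 10 per group (Sections 4.4 and 7), a two-sided 5% level, and the Kruskal-Wallis test.

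**Inputs assumed, because the protocol gives none.** A base rate of 1 episode per hour; usable hours normal within group with SD 1.2 (limited to 2-11 h); and overdispersion d of 0.1 to 0.25.

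**Model.** Count = Poisson(rate × hours × G), where G is a gamma variable with mean 1 and variance d. Kruskal-Wallis is applied once to the count and once to count ÷ hours.

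**The mechanism by hand.** Expected count = rate × mean hours.
- Equal rates of 1/h with mean hours 7, 6, 5, 4 from control to severe give expected counts of 7, 6, 5, 4. This is a gradient with no difference in rate.
- Rates of 1, 1.167, 1.4, 1.75 per hour over the same hours give 7 × 1 = 7, 6 × 1.167 = 7, 5 × 1.4 = 7 and 4 × 1.75 = 7. A 1.75-fold difference in rate disappears.

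**Simulation results.** The false-positive columns use equal rates of 1/h. The power columns use rates of 1, 1.25, 1.5 and 1.75 per hour. Ranges span d = 0.1 to 0.25 and, in the last row, three patterns of mean hours: 7/6.5/6/5, 7.5/6.5/5.5/4.5 and 7/6/5/4.

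| Mean hours, control to severe | False positives, count | False positives, rate | Power, count | Power, rate |
|---|---|---|---|---|
| Equal (7 h each) | 4-5% | 4-5% | 33-49% | 35-55% |
| 1 h fall (7/6.7/6.3/6) | 6-8% | 4-5% | 15-25% | 32-54% |
| 2-3 h fall | 12-38% | 4-5% | 4-11% | 27-49% |

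Each figure carries simulation error of a percentage point or two.

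**Sensitivity to the assumptions.** A separate simulation used base rates of 0.5 and 1 per hour, a within-group coefficient of variation of 15% in hours, and counts that were either pure Poisson or strongly overdispersed (d = 0.5). With hours falling as 7/6.3/5.6/4.9 or 7/6/5/4, raw counts rejected in 9-57% of null studies and rates in about 4-5%. With 7 h in every group (Poisson, 0.5/h), raw counts rejected in 4%. With the rates that equalise the counts over 7/6/5/4 h, power was 4-5% for counts and 13-70% for rates. Size depends heavily on the dispersion and on the gradient in hours; the pattern does not.

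**The case against.** **The bias is conditional.** A reader might infer that unequal hours will distort this outcome. The documents do not support that: they give no recording hours, no rate of signal loss and no link between usable time and severity. With equal mean hours the raw count keeps its error rate and loses only a little power. This objection stands, so the point is about what can happen.

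**The larger figures come from chosen scenarios.** A 2-3 h fall is large, and its direction is assumed. With a 1 h fall the excess of false positives is small, although power still drops by about half. So 12-38% is not an expected error rate, and no direction of bias can be predicted.

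**The analysis plan may settle it.** Normalising to recorded time is often left to a statistical analysis plan, and hypothesis 3.3(b) can be read as a rate. This has some force. However, the protocol itself names both the outcome and the tests and refers to Section 7 for the methods. Following its text compares counts.

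**Section 7 is not wrong.** A reader might conclude that the named tests must be replaced. They need not be: Kruskal-Wallis works on episodes per hour.

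**Item (c) has a second part.** The association of episodes with apneas and hypopneas is not affected.

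**There is some mitigation.** Overnight support, home visits and withdrawal when set-up is impossible (Section 4.2) remove some gross failures. They do not equalise hours.

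**Conclusion.** The point holds as a conditional weakness in the definition of one of five listed primary outcomes. Item 4.1.1(c) is a count with no denominator, compared between groups over whatever overlapping recording each person yields, while the hypothesis concerns frequency.

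The consequence ranges from negligible, if hours are similar across SRBD groups, to serious, if they fall by 2-3 h with severity. In that case most of the power for a 1.75-fold rate is lost and false positives rise well above 5%. Loss of power appears first: a 1 h fall already halves it. All these sizes rest on the assumed episode rate, dispersion and hours. Because the pattern of hours cannot be known beforehand and a rate costs almost nothing when hours are equal, the definition should be changed.

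**What to change.** In Section 4.1.1(c), define the between-group outcome as autonomic dysreflexia episodes per hour of valid simultaneous recording from the three devices, and report valid hours by SRBD group. Leave the part on association with apneas and hypopneas as it is.

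Section 7 can stay, with Kruskal-Wallis applied to the rate. A negative binomial model with log valid hours as offset is an optional alternative and would need a sentence there.

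The cost is a change of wording, with no added participants or assessments. Valid overlapping time must be derived from the device recordings; the protocol does not say in what form the devices provide it, so this should be confirmed. Rates from very short recordings will be noisier, and the hours reported by group will show how far that matters.

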### ***Sleep disorders after SCI***

A variety of sleep disorders have been described in individuals with SCI including insomnia and sleep-related breathing disorders (SRBDs). In a review of 11 epidemiological studies, the mean prevalence of SRBDs was 6% in men and 4% in women in the general population. In comparison, SRBDs have been reported in 48% to 91% of individuals with tetraplegia, and 13% to 63% of individuals with paraplegia. Although the frequency of SRBDs after SCI is much greater than in the able-bodied population, this is still a largely under-studied secondary condition in the SCI population.

Untreated sleep-related breathing disorders as an aggravating factor for neuropathic pain, cardiovascular dysfunction and spasticity following spinal cord injury

In a recent qualitative study, 20 individuals with SCI voiced several barriers to good quality sleep including SCI-related dysfunction, care, sleep environment, pain, anxiety, and avoidance. In summary, “sleep problems, such as those described by participants in this study, have the potential to exacerbate several conditions that commonly occur after SCI and to significantly affect health-related quality of life.”

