### ***Spasticity and sleep disorders***

Similar to neuropathic pain, spasticity is a common secondary complication after SCI that has been reported 40% to 60% of the individuals living with tetraplegia. It is still unclear how spinal cord injured people with an underlying sympathetic overactivity due to the loss of supraspinal control respond to those sympathetic and catecholaminergic changes during and after hypoxia. Also, the effects of sleep-related hypoxia on the sympathetically-denervated muscles of individuals with SCI remain unknown. Prior studies revealed an increased muscle sympathetic nerve activity under hypoxic conditions, which persisted even after removal of acute short-term exposure to intermittent hypoxia. While a previous study showed that muscle oxygenation is not significantly affected by intermittent hypoxia exposure, the prefrontal cortex suffered detrimental effects of hypoxia in the prefrontal cortex in able-bodied individuals. One may speculate that anterior horn cells may also be vulnerable to hypoxia and, hence, the response of the low motor neurons caudal to SCI may overreact (or underreact) to hypoxia and sympathetic drive. Of note, a recent systematic review on the physiologic and psychologic triggers for spasticity exacerbation found no previous study on the effects of SRBDs on the spasticity in individuals with SCI. Nonetheless, the potential effects of untreated SRBDs on the degree of spasticity after SCI have never been properly examined.

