- (d) At discretion and expenses of the research assistant and [name] (co-investigator at Sunnybrook Health Science Centre, the home-based sleep study devices can be either send by especial and secure courier (e.g. FEDEX) or picked up by the research assistant at the study participant's residence on next the day after the test. The study participant must agree with the latter option before the research assistant can drop by their residence. All the costs for either option are included in the price for the service as per the revised inter-institutional agreement.
- (e) The research assistant must properly destroy all PHI right after completing of the home-based sleep studies. The only information that should be maintained includes the study participant ID number and data on how many times and the reasons for phone calls and/or visit to provide technical support.

(2) Individuals living with SCI are often on pharmacologic treatment for neuropathic pain and/or spasticity. Given their potential confounding effect, we will collect information on the medicaments taken at the time of the studies in order to properly analyze the results of both studies.

(3) All the laboratory blood tests will be carried out by a company that provides high-quality services using standardized assays and methods across Canada. This will facilitate the comparisons and interpretation of the results from this research project.

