Those individuals with clinical warning signs for SRBDs will undergo a home-based sleep study using the ApneaLink™ (Picture 1) device to confirm the diagnosis of SRBD (n=30). Based on the results of the home-based sleep study, individuals with SRBD will be grouped into mild (n=10), moderate (n=10) and severe sleep apnea (n=10). Also, individuals without clinical warning signs for SRBD will undergo a home-based sleep study using ApneaLink™ in order to identify 10 study participants without SRBDs (“control cases”).

All participants will also undergo cardiovascular evaluation during sleep using the Bittium Faros™ 180 (Picture 3) and Caretaker™ Medical cNIBP monitor (Picture 2) devices to assess sympathetic activity during sleep in all study participants (n=40). All participants will be examined with regards to their degree of spasticity as assessed using the Modified Ashworth Scale. Also, all participants will undergo laboratory blood tests to measure their serum CRP level.

Furthermore, an economic analysis will be undertaken in order to compare the costs of the home-based sleep study with the conventional polysomnography in a sleep clinic. For this purpose, the costs of the home-based sleep test will be estimated based on our experience during this study. The costs of the conventional polysomnography will be obtained from the sleep clinic at Sunnybrook Hospital where [name], co-investigator in this study, works. The professional and technical fees will be derived from the Ontario Health Insurance Plan (OHIP) – Schedule of Benefits, Physician Services.

All participants who are diagnosed with moderate-to-severe SRBDs during the study will be referred to [name] or other sleep specialist for consultation and CPAP therapy. Also, study participants whose CRP levels are greater than 10 mg/L (normal range up to 3 mg/L) will be immediately referred to their family physician (or emergency if symptoms or signs of systemic infection) for further investigations and treatment because a CRP greater than 10 mg/L is suggestive of infection or primary inflammatory disease.

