### **5.0 Selection of Subjects**

#### **5.1 Inclusion Criteria**

To take part in this study participant must:

- Have traumatic or nontraumatic (without risk for disease recurrence) cervical/thoracic (injury level at C1 to T6), complete/incomplete (AIS A, B, C or D) SCI who were not previously diagnosed and treated for sleep apnea.
- English-speaking adults 18 years of age or older
- At least 2 months after injury

Untreated sleep-related breathing disorders as an aggravating factor for neuropathic pain, cardiovascular dysfunction and spasticity following spinal cord injury

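### Upper-limb spasticity is compared across all C1 to T6 participants without regard to injury level, so an association with SRBD can arise from injury level alone

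*Protocol*

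**What the plan says.** Protocol 4.1.1(d) lists as a primary outcome "The degree of spasticity in the upper and lower limbs as assessed using the Modified Ashworth Scale". Section 4.3 applies it to the whole sample: "All participants will be examined with regards to their degree of spasticity as assessed using the Modified Ashworth Scale". Section 5.1 admits "cervical/thoracic (injury level at C1 to T6), complete/incomplete (AIS A, B, C or D) SCI", so tetraplegia and high paraplegia are mixed.

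Hypothesis (c) in 3.3 is that "Individuals with SCI and untreated SRBDs more frequently develop more severe spasticity". Section 7 tests outcomes across the four groups (no, mild, moderate and severe SRBD) by Kruskal-Wallis or ANOVA, with Fisher's exact test for categorical variables. It names no stratification, restriction or adjustment by injury level. The only confounder the protocol names is drug treatment, in 4.2: "Given their potential confounding effect, we will collect information on the medicaments taken at the time of the studies".

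The background in 2.1 ties SRBD to level: "SRBDs have been reported in 48% to 91% of individuals with tetraplegia, and 13% to 63% of individuals with paraplegia". Nothing limits upper-limb scoring to cervical injuries, and nothing says whether arm and leg scores are kept apart or combined.

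**The concern.** In an injury below the arm segments, the nerve supply to the arms lies above the lesion. An upper-limb Ashworth score of 0 in such a participant does not mean that a limb at risk escaped spasticity; the injury could hardly have produced any. This is general anatomy and is not stated in the protocol.

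If these near-structural zeros were spread evenly over the SRBD groups, they would only dilute the comparison. The ranges in 2.1 suggest they are not: thoracic participants have SRBD less often, so they tend to collect among the controls. The arms of the SRBD groups would then look more spastic with no SRBD effect at all, which is the pattern hypothesis (c) predicts. At stake is whether a positive finding for the third primary objective could be told apart from a difference in injury level.

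**Working it through.** The protocol gives no sample size, power or expected rate for the spasticity comparison, so there is no figure to reproduce. Its 10 per group is derived for VAS pain and serves here only as a group size.

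**Inputs from the protocol**
- SRBD in tetraplegia, t: 48% to 91%; midpoint (48 + 91)/2 = 69.5%.
- SRBD in paraplegia, p: 13% to 63%; midpoint (13 + 63)/2 = 38%.
- Spasticity in tetraplegia: 40% to 60% (background on spasticity and sleep disorders). This is spasticity overall, not of the arm.
- Group size: minimum 10 (4.4). With 70 invited, 70/4 = 17.5, so 17 per group is taken as the upper case.

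**Assumptions not in the protocol**
- Half of recruits are cervical.
- Arm spasticity occurs in 50% of cervical and 0% of thoracic participants.
- When spasticity is present, grades 1 to 4 are equally likely.
- The three SRBD groups share one cervical fraction.
- SRBD has no effect on spasticity once level is given.

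**Step 1: cervical share by SRBD status (Bayes' rule, 50:50 mix)**

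With SRBD: t/(t + p). Without: (1 − t)/[(1 − t) + (1 − p)].

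At the midpoints: 0.695/(0.695 + 0.38) = 0.647 with SRBD, and 0.305/(0.305 + 0.62) = 0.330 without.

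**Step 2: apparent arm spasticity**

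Multiply each share by 0.5. At the midpoints: 0.647 × 0.5 = 32% with SRBD and 0.330 × 0.5 = 16% without, although SRBD does nothing.

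**Step 3: false-positive rate of the planned test**

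The four-group Kruskal-Wallis test at 5% was simulated on the upper-limb score, with 6,000 trials per scenario. Repeated runs differ by about a percentage point.

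| t / p | Cervical share, SRBD v none | Apparent arm spasticity | Rejection, 10 per group | Rejection, 17 per group |
|---|---|---|---|---|
| 69.5% / 38% (mid) | 65% v 33% | 32% v 16% | 8–9% | 13–14% |
| 48% / 13% (both low) | 79% v 37% | 39% v 19% | 11–12% | about 19% |
| 91% / 63% (both high) | 59% v 20% | 30% v 10% | 11–12% | 21–23% |
| 48% / 63% (reversed) | 43% v 58% | 22% v 29% | 5–6% | 7% |
| 91% / 13% (widest) | 87% v 9% | 44% v 5% | 39–41% | 77% |
| equal level mix | 50% v 50% | 25% v 25% | 4% | 4–5% |

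**Step 4: sensitivity**
- Letting arm spasticity in cervical injuries run from 40% to 60% gives 6.6% to 10.5% (10 per group) and 10% to 17% (17 per group) at the midpoints. For the both-high pair it gives 9% to 15% and 15% to 28%.
- Assuming 60% cervical recruits instead of 50% changes little.
- If arm and leg scores are summed, with leg spasticity assumed in 50% at every level, the first three pairs give about 6% to 7% at 10 per group and 7% to 9% at 17 per group.

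The equal-mix row shows that level is the whole source of the excess. The excess grows with group size, so recruiting beyond the minimum makes it worse.

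**The case against.** The strongest reply is that 4.1.1(d) names the limbs examined, not a score. Muscle groups, limb summaries and analysis subsets are often left to a statistical analysis plan, and separate reporting of arms and legs would fit the text. That stands in part. A reader might infer that the protocol pools arms and legs; it does not say so, and a summed score would show much less inflation. But the outcome, the population scored and the unadjusted tests are all fixed in the protocol. A separate upper-limb comparison across everyone, which the text equally allows, is the worse case.

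A reader might also infer that controls must score lower by construction. The documents do not support that: the two SRBD ranges overlap, and at 48%/63% the direction reverses. The stated direction is the likelier one only because both ends of the paraplegia range lie lower.

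Nor are arm scores zero for every thoracic injury, since T1 still supplies hand muscles; about T2 to T6 is the safe statement. Cervical arms can vary with SRBD, so the upper-limb score is not merely a marker of level. The lower-limb part is not a structural zero at any eligible level, so the whole outcome is not invalidated.

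On size, a two-group rank test of 30 SRBD participants against 10 controls rejects in about 11% to 18% of null trials. That is not the test in Section 7; the four-group test at 10 per group gives less.

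Finally, this can be called ordinary confounding by level, curable by adjustment. Adjustment or stratification does deal with the false positives, but thoracic arms would still carry no information on the third objective. Section 7's comparison of baseline characteristics might reveal a level imbalance; it would not correct for one.

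**Conclusion.** The point holds in a limited form and should be corrected. Followed as written, the plan permits an all-participant upper-limb comparison in which arms that could hardly become spastic are likely to be unevenly spread over the SRBD groups, with nothing in Section 7 to deal with it.

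Under the stated assumptions the false-positive rate is about 8% to 12% at 10 per group and about 14% to 22% at 17 per group for the mid, both-low and both-high pairs, against a nominal 5%. Over the full corners of the protocol's ranges it runs from near nominal with reversed direction to about 40% and 77%. These sizes rest on an assumed cervical share, an assumed grade distribution, and an arm-spasticity rate borrowed from a figure for spasticity overall in tetraplegia. If arm spasticity is rarer than that, the inflation is smaller. The mechanism is secure; its size, and to a lesser degree its direction, are not.

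**What to change.** Amend 4.1.1(d) and add a sentence to Section 7:
- Compare the lower-limb Modified Ashworth score across the SRBD groups in all participants.
- Analyse the upper-limb score separately, in participants with a cervical level only.
- Do not sum upper- and lower-limb scores across injury levels.
- Stratify or adjust the spasticity comparison by injury level (cervical v thoracic). This includes the lower-limb comparison, because the protocol gives no ground for assuming that leg spasticity is equally common at all levels.

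The examination and data collection do not change, and level is already recorded because eligibility depends on it. The cost is a short amendment and fewer participants in the upper-limb comparison; those left out carry essentially no information on it.
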